### Recruitment

Unique codes will be assigned to perform allocation concealment and prevent “selection bias". Supplements and placebos capsules will be provided in the same appearance (in terms of color and shape) and packed in similar bottles. The bottles will be labeled with different marks (A and B) and placed in envelopes with serial numbers by someone not related to the study. Participants and researchers will not be aware of the bottles content. Intervention groups will also receive diets from a nutritionist who is not involved in this study.

The participants will be assigned to 4 groups according to the method of stratified permuted block randomization based on treatment conditions and BMI (BMI: 18.5-25 and BMI 
≥
 25), in equal block sizes of 4. The random allocation list will be created by Package `blockrand' in R software, version 4.0.2.

Randomization and allocation will be concealed from participants and researchers until finishing the study steps and data analysis. An independent biostatistician will generate the allocation sequence. 2 midwifes will give consecutive numbers to the eligible participants and refer them to a nutritionist. The sealed envelope containing the treatment code will be opened by the supervisor, after analyzing the final data or in an emergency condition.

All trial healthcare providers, data analysts, and outcome assessors will be blinded to intervention assignments. Participants may only be aware of the type of diet but will not be aware of the placebo or curcumin supplement content.

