**Materials and Methods:**

96 infertile women with PCOS, aged 18-40 yr, will participate in this randomized, placebo-controlled clinical trial. Based on treatment conditions and body mass index, the participants will be randomly divided into 4 equal groups using a randomized block design. They will receive a DASH or standard diet containing 52% carbohydrate, 18% protein, and 30% total fat, with the same prescribed sodium, plus 500 mg twice daily curcumin or placebo for 12 wk. The mRNA expression of *IL-1
α

*, *5
α

* reductase, and androgenic and glycemic profiles will be measured at baseline and at the end of the study.

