### Interventions

Participants will be given 2 capsules of curcumin supplement per day (1 after breakfast and another after an evening meal with water) or 2 placebo capsules of curcumin per day at the same time for 12 wk. Curcumin capsules (BCM95/Curcugreen) and their placebos, with the same texture and appearance, were produced as 500 mg zero size veg capsules by “M/s Arjuna Natural Pvt Ltd., India”. The curcumin supplement was made from dried turmeric rhizomes by extraction with ethyl acetate. *Curcuma longa L. *commonly known as turmeric contains curcuminoids (curcumin, demethoxy curcumin, and bisdemethoxy curcumin) and essential oil of turmeric (ar-turmerone, curlone, and ar-curcumene). Curcuminoids are specific compounds with medicinal properties, of which the most important and active ingredient is the yellow coloring pigment curcumin; Ar-turmerone (the main bioactive components of the *Curcuma longa L*. essential oil), inhibits the P-glycoprotein pathway, thus improving the oral bioavailability and bioactivity of orally administered curcuminoids. BCM-95 was characterized by 95% total curcuminoid complex; the final formulation containing at least 65% curcumin and 86% total curcuminoids; and the essential oil containing not less than 45% ar-turmerone. Each 500-mg capsule contained 475 mg of curcuminoids and the essential oil of natural turmeric. Each placebo capsule contained 500 mg of roasted rice powder. The curcumin capsule actives will be analyzed by HPLC, heavy metals by ICP-MS; residual solvents by GCHS, pesticides by GCMS, and microbial indicators all of which were ensured to be in line with the EU standards (regulation (EC) No 1881/2006; directive 2009/32/CE; regulation (EC) No. 396/2005 and related amendments).

The intervention groups will receive 2 healthy dietary patterns (DASH or standard diet). These diets will be designed in the form of an individual diet containing 18% protein, 52% carbohydrates, and 30% total fat, which will be matched with the macronutrient plan used in the other original trial (23). Dietary programs will be planned after baseline assessments based on the current dietary intakes and body weight of each person. Daily calorie requirements will be estimated by calculating the resting energy expenditure and physical activity levels. If a person was overweight (BMI is 25.0 to 
<
 30.0 kg/m²) or obese (
≥

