 day of visit), each bottle containing 64 capsules (providing supplement for 1 month and a grace period of 2 days). Administration instructions on taking the pills and what needs to be done in case a dose is missed were set for patients, including taking 2 curcumin/placebo capsules a day (one after breakfast and one after an evening meal with water) and taking the missed capsule the same day. The patients will be monitored for daily supplementations by contacting them via phone interviews and messaging (Eitaa or Bale apps) twice a day. Moreover, daily consumption of supplements/placebos will be recorded in the case report form given to participants. At each follow-up visit, a nutritionist will assess the participants adherence to the diet and supplementation. The number of capsules taken will be calculated by counting the remaining capsules in each bottle. If the number of unused prescription capsules is more than 12 out of 60 capsules per month, for each participant, that patient will be classified in the non-adherent group.

All adverse events including unfavorable and/or unintended signs and any undesirable experience occurring to a patient will be reported in writing to the Medical Ethics Committee and the Data Monitoring Committee of the Shahid Sadoughi University of Medical Sciences, Yazd, Iran. The participants, for whatever reason, can discontinue participating in the research study at any given time before or after signing the consent form. The researcher may also terminate the study to maintain safety and protect the participant from excessive risks and/or to keep the integrity of the research data due to inappropriate follow-up by the participant. In case of termination of the study by the investigator, the reasons for the termination will be explained to the participants.

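### With only two bottle marks, A and B, one emergency code opening can reveal curcumin versus placebo for other women, potentially all 96, to anyone who sees their marks

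*Protocol article*

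**What the plan says.** The labelling rule is in the Recruitment section of the protocol article: "The bottles will be labeled with different marks (A and B) and placed in envelopes with serial numbers". Someone unrelated to the study does this. The serial number belongs to the envelope; the mark on the bottle itself is A or B. The section opens with a separate device, "Unique codes will be assigned to perform allocation concealment", but does not say how these codes relate to the letters.

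On code breaking: "The sealed envelope containing the treatment code will be opened by the supervisor, after analyzing the final data or in an emergency condition".

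On masking: "All trial healthcare providers, data analysts, and outcome assessors will be blinded to intervention assignments". The section also states that participants and researchers will not know what the bottles contain, and that allocation stays hidden until study procedures and analysis are complete. Participants may know their diet but not their capsule.

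The Interventions section has each woman receive a bottle on days 1, 30 and 60. It bases supplement adherence on returned capsules: "The number of capsules taken will be calculated by counting the remaining capsules in each bottle".

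**The concern.** A mask built on one letter per arm fails as a whole. Once anyone learns what a single bottle holds, the meaning of A and B is known for every bottle in the trial. The article provides a legitimate route to that event, the emergency opening, and that route can be used while women are still being recruited and followed. People who handle many women's bottles would then know the supplement arm of women already enrolled and of women still to come.

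At stake is the masked comparison of curcumin with placebo. Staff who know the arm may, without intending to, counsel, encourage or retain women differently. That could affect co-intervention, drop-out, and who remains in the per-protocol analysis.

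**Working it through.** **Inputs**
- Marks on bottles: 2, A and B (Recruitment).
- Capsule contents: 2, curcumin and placebo (Trial design; Interventions).
- Total: "96 infertile women with PCOS, aged 18-40 yr, will participate in this randomized, placebo-controlled clinical trial" (Abstract).
- Allocation: "the participants will be randomly divided into 4 equal groups using a randomized block design" (Abstract), with 24 per group (Sample size).
- Bottles per woman: 3, on days 1, 30 and 60 (Interventions).

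**Step 1. Reproduce the plan's total.** 4 groups × 24 = 96.

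**Step 2. Women per letter.** Two of the four groups take curcumin and two take placebo: 2 × 24 = 48 under each letter.

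**Step 3. What one disclosure reveals.** With two marks and two contents the mapping is one-to-one. If one bottle marked A is found to hold a given content, all A bottles hold it and all B bottles hold the other. Beyond the woman concerned, this decodes 47 women with the same letter and 48 with the other letter: 47 + 48 = 95, so 96 in total. It does not matter whether the opened envelope is a master list or one woman's code, because her letter is enough.

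**Step 4. How the number of marks changes this.** With k marks per content (k ≥ 2) and 48 women per content, one disclosure directly identifies the 48/k − 1 other women who share that mark.

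| Marks in total | Marks per content | Other women directly decoded |
|---|---|---|
| 2 (as planned) | 1 | 95 |
| 4 | 2 | 48/2 − 1 = 23 |
| 8 | 4 | 48/4 − 1 = 11 |
| 16 | 8 | 48/8 − 1 = 5 |
| 96 (unique) | 48 | 48/48 − 1 = 0 |

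**Step 5. Who can use the disclosure.** It decodes other women only for someone who also sees their marks. On the article's text that includes whoever counts the capsules left in each bottle. It can also include the supervisor who opens the envelope, and an analyst if the data are coded A/B. It does not include a woman who sees only her own bottles.

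**Step 6. Do the other safeguards remove the letter?** The serial numbers are on the envelopes, and the bottle has to come out to be used. The unique codes are assigned for allocation concealment, which protects the assignment before it is made. Neither is said to replace or cover the A/B mark.

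**The case against.** Several points on the other side are sound.

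- **Outcomes.** Both primary outcomes are real-time PCR measurements, and the glycaemic and androgen outcomes are laboratory assays or are calculated from them. Knowing the arm has little room to affect these readings.
- **Adherence and analysis.** Supplement non-adherence is set by a count, more than 12 of 60 capsules unused in a month, not by opinion. An intention-to-treat analysis that disregards non-compliance and withdrawal is planned beside the per-protocol one.
- **Condensed text.** This is a journal article, and the detailed code-break procedure may sit in a fuller document. The two-letter bottle mark, however, is a rule the article states, not a detail it leaves out.

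A reader might also infer more than the documents support:

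- **That a correct guess by one woman unmasks everyone.** It reveals her own arm only, unless letters are shared or seen by others.
- **That the capsules can be told apart by smell or content.** The active capsule holds a yellow pigment and turmeric oil, and for the comparator "Each placebo capsule contained 500 mg of roasted rice powder". But the article says the capsules match in texture, appearance, colour and shape, and says nothing about odour. Opening a capsule would unmask that woman under any labelling scheme.
- **That there is one master envelope.** The wording does not settle this, and the point does not need it.
- **That curcumin is the only factor that can be masked.** Providers, analysts and assessors are to be blinded to intervention assignments generally, and the dietitian reviewing food records is blind to allocation. Only participants are acknowledged as possibly knowing their diet.
- **That the staff who contact women twice a day see the bottles.** The article does not say so.

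These limits reduce the size of the concern. They leave the shared letter itself unanswered.

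**Conclusion.** The point holds as a weakness in the masking that is cheap to remove. A single permitted code opening would decode both letters for anyone who sees other women's marks, with a ceiling of 96 women (48 per letter), against 1 under unique numbering. This works against the article's own aim of concealment until the analysis is complete.

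The figure of 96 is an upper limit, not an expected effect. It assumes four full groups of 24, a letter meaning that stays the same throughout the trial, and an observer who sees every mark. It also assumes that the letter stays on the bottle when staff handle it, which the text implies but does not spell out. Nothing in the article says that the result of an opening would be passed to the capsule counters.

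The likely bias is modest and would run mainly through co-intervention, retention and the make-up of the per-protocol set, not through the assays.

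**What to change.** Have the independent person who already labels the bottles put a unique number for each woman, taken from the randomisation list, on all three of her bottles. No A/B or other shared arm mark should appear on anything that the site or the woman sees. Hold one sealed code per number, so that the emergency provision stays available but an opening reveals only the woman concerned. Give the analysts a dummy arm code, and only in the final dataset. State in the Recruitment section how the unique codes, envelope serial numbers and bottle labels relate to one another.

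The cost is labels for 96 × 3 = 288 bottles (over-labels if they are already marked) and 96 code slips. No extra visits, staff or participants are needed.

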## 2. Materials and Methods

### Trial design and study setting

This randomized, placebo-controlled clinical trial will be conducted on PCOS women candidates for in vitro fertilization (IVF), using a convenience sampling method. Participants in a 2
×
2 factorial design will be randomly divided into 4 parallel treatment groups using block randomization: (1) curcumin supplement + DASH diet (2) curcumin supplement + standard diet (3) placebo + DASH diet, and (4) placebo + standard diet. The follow-up duration will be 12 wk. The study will be conducted at the Yazd Reproductive Sciences Institute, Shahid Sadoughi University of Medical Sciences, Yazd, Iran. An overview of the study is presented in figure 1.

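### Fixed, published blocks of 4 for four arms, with diet unmasked, allow up to a third of diet allocations to be known in advance by anyone who learns the earlier ones

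*Protocol article*

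**What the plan says.** All references are to the protocol article.

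- **Arms and ratio.** Under Trial design and study setting, women in a 2 × 2 factorial design are "randomly divided into 4 parallel treatment groups using block randomization". The abstract makes the arms equal: "the participants will be randomly divided into 4 equal groups using a randomized block design".
- **Method.** Under Recruitment: "The participants will be assigned to 4 groups according to the method of stratified permuted block randomization", with BMI 18.5-25 and BMI ≥ 25 as strata and allocation "in equal block sizes of 4". No variation in block size is mentioned.
- **Masking.** The capsules are masked but the diet is not: "Participants may only be aware of the type of diet but will not be aware of the placebo or curcumin supplement content". The bottles carry a mark, A or B.
- **Who sees diet.** Under Interventions, counselling on the assigned diet is face to face, and "At each follow-up visit, a nutritionist will assess the participants adherence to the diet and supplementation".
- **Safeguards.** Recruitment names an independent biostatistician who generates the list, numbered envelopes prepared by someone unrelated to the study, a nutritionist outside the study who gives the diets, and two midwives who number eligible women consecutively and refer them. It states that allocation is concealed from participants and researchers until the analysis, and that concealment is meant to prevent selection bias.

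**The concern.** With equal allocation to four arms, 4 is the smallest possible block. At that size the end of every block is determined by its beginning. This matters little when both factors are masked, but here one of the two randomised factors is visible once it has been assigned. The trial runs at one institute with convenience sampling, a woman's BMI stratum is known when she is enrolled, and the block size is in print. Someone who follows the diets already given in a stratum can count through the block.

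The comparison at stake is DASH versus standard diet. If a recruiter expected the next place to be a particular diet, a woman thought more or less likely to keep to it could be brought forward or held back. With 24 women per arm, a few such choices could matter. Adjustment by ANCOVA does not reach characteristics that are not measured, such as motivation.

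**Working it through.** The plan gives no figure for predictability, so there is none to reproduce.

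**Inputs.** Four arms at 1:1:1:1 (Trial design; abstract); fixed block size 4 and BMI strata (Recruitment); 96 women (abstract), hence 96 / 4 = 24 blocks if both strata end on a complete block.

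**1. Content of a block.** Four places and four equally frequent arms put each arm in once. By diet, a block holds two DASH and two standard places.

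**2. Diet known with certainty.** A diet is known in advance when all places left in the block carry the same diet. Over the 24 orders of the four arms, the probability by position is:

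| Position | 1 | 2 | 3 | 4 |
|---|---|---|---|---|
| Diet certain | 0 | 0 | 1/3 | 1 |

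Expected number per block = 0 + 0 + 1/3 + 1 = 4/3, and (4/3) / 4 = 33.3%. Over 96 women that is 32. One place is certain in 16 of the 24 orders and two places in the other 8. The general formula, with m places per diet in a block, is 1/(m + 1); for m = 2 it gives 1/3.

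**3. Best guess of diet.** The more frequent remaining diet is right with probability 1/2, 2/3, 2/3 and 1 at positions 1 to 4 (position 3: 2/3 × 1/2 + 1/3 × 1 = 2/3). The mean is (1/2 + 2/3 + 2/3 + 1) / 4 = 17/24 = 70.8%, against 50% by chance.

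**4. If bottle marks were also seen.** The last place of each block would be certain (1/4 = 25%). The best guess of diet plus mark would be right (1/4 + 1/3 + 1/2 + 1) / 4 = 52% of the time, against 25% by chance. This identifies a coded arm only.

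**5. Effect of varying the block size.** Simulation with an assumed 48 women per stratum and 4,000 runs. The guesser knows the candidate sizes and all earlier diets, but not where blocks end.

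| Block sizes | Diet certain | Best guess of diet |
|---|---|---|
| 4, fixed | 33.3% | 71% |
| 4 and 8, random | about 7% | about 68% |
| 4, 8 and 12, random | about 2.5% | about 66% |

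Larger fixed blocks do less: 1/5 = 20% for size 8 and 1/7 = 14.3% for size 12.

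**6. Cost in balance.** If a stratum stops inside a block, the largest possible difference between arm sizes is the number of times each arm appears in that block: 1 for size 4, 2 for size 8, 3 for size 12. In a simulated stratum of 22 women (an assumed size), the mean difference between largest and smallest arm is 1.0 with fixed 4, 1.1 with 4/8 and 1.2 with 4/8/12.

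**The case against.** The strongest answer is that the route to bias is not documented. The 33% requires a person who influences enrolment, knows every earlier diet in that stratum in order, and knows where blocks start. The Recruitment section separates these roles, and the midwives are described only as numbering and referring women. The sentence on visibility of diet concerns participants, not recruiters. The primary outcomes are laboratory measures of gene expression, BMI is already stratified, and no perceptible characteristic has been shown to predict the change in expression beyond BMI. All of this stands, and it makes the figures a ceiling.

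It does not remove the point. Codes, envelopes and an independent statistician protect the list; they do not stop someone deducing its next entry from earlier allocations that are in the open. Participants know their diet, and a nutritionist checks adherence to it at every follow-up visit, so the information circulates at the site.

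Two stronger readings are tempting and not supported:

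- **That concealment has failed, or that a third of allocations will be known.** The article does not say that the midwives see diets, and the calculation shows what could be known, not what will be used.
- **That the whole treatment arm, including curcumin, is predictable.** Nothing says recruiters see the bottle marks. If they did, A or B would not tell them which is curcumin, so the 25% and 52% figures give no usable foreknowledge of the supplement.

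It is also fair to say that varying the blocks does little for best-guess accuracy (71% to 66-68%). Its benefit is in removing most of the certainty.

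**Conclusion.** The point holds as a conditional weakness in a stated design choice. Fixed blocks of 4 let a person with full knowledge of a stratum's earlier diets be certain of up to one third of diet allocations (at most about 32 of 96) and guess 71% correctly. The one third is an average over blocks, each of which yields one or two certain places of four.

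It rests on equal allocation, on BMI as the only stratifier, and on strata that end on, or close to, a complete block. It also assumes that the person knows the order of earlier diets and the block boundaries, which the article neither states nor rules out. The exposure is mainly in DASH versus standard diet; curcumin versus placebo remains protected by the masked capsules. No bias in the estimated effect has been quantified, and the weakness does not by itself invalidate the trial. The change is worth making because it is cheap.

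**What to change.** For women not yet randomised, generate the remaining list with block sizes that vary at random within each BMI stratum, for example 4 and 8, or 4, 8 and 12. The independent biostatistician alone should hold the sizes and the list, and the sizes should not appear in documents that recruiting staff use. It would also help to state that those who enrol women have no access to earlier diet assignments or bottle marks.

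Arms, sample size and analysis stay as they are. The cost is slightly more imbalance where a stratum stops inside a block: a largest possible difference between arms of 2 with 4/8, or 3 with 4/8/12, against 1 now. The article itself expects few women in the 18.5-25 stratum (Study strengths and limitations). If that stratum is small, 4/8 is the better choice, since it already brings certain diet allocations from 33% to about 7%.

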### Statistical methods

The values of quantitative variables will be presented as the mean 
±
 standard deviation, and qualitative variables will be expressed as numbers and percentages. The normality of data will be examined by the Kolmogorov-Smirnov test.

The frequency among study groups will be compared using the Chi-square test. Independent sample *t* test and 2-way ANOVA will be applied to estimate the mean of quantitative variable changes and interactions between study groups; Bonferroni correction will be considered for multiple comparisons; and analysis of covariance (ANCOVA) will be used to compare the differences in the mean of quantitative data between the studied groups, while taking into account the influence of possible confounding variables. Before statistical analysis, all data will be checked for accuracy and completeness. All statistical analysis will be conducted using SPSS 22 (SPSS, Inc, Chicago, IL, USA). A p-value 
<
 0.05 will be defined as a statistically significant level.

The “intention-to-treat" and “per protocol analysis" approaches will be performed for data analysis. The “intention-to-treat" analysis considers all participants in their main randomized groups, regardless of whether they follow the prescribed intervention according to the protocol or not, and also ignores non-compliance and withdrawal. Per protocol analysis, which accurately reflects what has been done, will be conducted based on actual adherence to the interventions.

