### Sample size

The sample size of 24 in each group was determined according to α = 0.05, the power of 80%, dropout rate of 20%, and considering a minimal clinically important difference of 0.969 and an effect size of 1, based on Heshmati et al. study (21) using the following formula: 

$$n=\frac{{\left(Z_{1-\alpha /2}+Z_{1-\beta }\right)}^{2}\left(S_{1}^{2}+S_{2}^{2}\right)}{{\left(\mu_{1}-\mu_{2}\right)}^{2}}$$

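### No primary model is named for the two gene-expression outcomes, and neither the baseline value nor the BMI stratum is a stated covariate; the change-score tests are valid but less precise than a baseline-adjusted ANCOVA

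*Protocol article*

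**What the plan says.** The trial is a 2×2 factorial with four groups of 24. Its two primary outcomes are the expression of the IL-1α and 5α-reductase genes (protocol article, Trial design and study setting; Outcomes; Sample size).

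For continuous outcomes, Statistical methods lists:

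- an independent t test and two-way ANOVA on changes: "2-way ANOVA will be applied to estimate the mean of quantitative variable changes and interactions between study groups". This is the only place where the section mentions an interaction.
- an ANCOVA comparing group means, "while taking into account the influence of possible confounding variables". No covariate is named.

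The section does not rank these methods and does not tie any of them to the primary outcomes.

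Two other places bear on the choice of model. The Abstract says that the two mRNA measures and the "androgenic and glycemic profiles will be measured at baseline and at the end of the study", so a baseline value of each primary outcome will exist. The Recruitment section describes "stratified permuted block randomization based on treatment conditions and BMI", with strata of 18.5–25 and 25 or more.

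**The concern.** Three overlapping methods are listed without a stated order, so the result that counts for each primary outcome is not fixed. Two features of the listed methods also matter.

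**Precision.** A change score uses the baseline with its slope fixed at 1. ANCOVA estimates that slope and so is usually more precise. The interaction, which a factorial design needs in order to be read, is placed with the less precise method.

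**Covariates.** Confounding is not the right criterion for choosing covariates in a randomised comparison. The natural choices are the outcome's own baseline value and the factor used to stratify the randomisation, and neither is named. The criterion as worded also does not limit covariates to variables measured before randomisation.

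At stake are precision and pre-specification in a trial that expects about 19 evaluable patients per group.

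**Working it through.** **The plan's own sample size.** The Sample size section says: "The sample size of 24 in each group was determined according to α = 0.05, the power of 80%, dropout rate of 20" per cent, "considering a minimal clinically important difference of 0.969 and an effect size of 1". The printed formula is two-sided.

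- Effect size 1: n = 2 × (1.960 + 0.842)² / 1² = 15.7, so 16; 16/0.8 = 20 per group.
- Difference 0.969 with SD 1 (effect size rounded to 1): n = 16.7, so 17; 17/0.8 = 21.25, so 22.
- The exact t test gives 17, so 22, for an effect of 1, and 18, so 23, for 0.969.

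The stated 24 is above all of these. That is a separate matter and does not affect this point. Evaluable patients: 24 × 0.8 = 19.2, taken as 19 per group.

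**Change score against ANCOVA.** Let σ² be the variance of one measurement, equal at both visits, and ρ the correlation between baseline and week 12. In large samples:

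- Var(change) = 2σ²(1−ρ)
- Var(ANCOVA) = σ²(1−ρ²)
- Ratio ANCOVA/change = (1−ρ²)/[2(1−ρ)] = (1+ρ)/2

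The protocol gives no ρ, so a range is assumed. Power is for two groups of 19, two-sided 5%: Φ(δ/[SD × √(2/19)] − 1.96). In columns 4 and 5 the effect is 1 SD of a single measurement. In column 6 it is 1 SD of the change.

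| ρ | Variance ratio | Patients needed, change v ANCOVA | Power, change | Power, ANCOVA | Power, ANCOVA, if SD is of the change |
|---|---|---|---|---|---|
| 0.3 | 0.65 | 1.54 times | 74.1% | 89.8% | 96.9% |
| 0.5 | 0.75 | 1.33 times | 86.9% | 94.5% | 94.5% |
| 0.7 | 0.85 | 1.18 times | 97.8% | 99.1% | 91.7% |
| 0.9 | 0.95 | 1.05 times | about 100% | about 100% | 88.5% |

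Where the SD is that of the change, change-score power is 86.9% at every ρ. Below ρ = 0.5, 2(1−ρ) exceeds 1, so the change score is less precise than the week-12 value alone.

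Estimating the baseline slope costs little: 4 × 19 = 76 patients less 4 cell means leaves 72 residual degrees of freedom, and slope plus stratum take 2 of them.

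**Chance imbalance.** If one group starts d higher at baseline, the change-score difference shifts by −(1−ρ)d. One standard error of d between two cells is √(2/19) = 0.32 SD. At ρ = 0.5 the shift is 0.16 SD. It averages to zero over randomisations, and ANCOVA corrects for it in the trial at hand.

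**Leaving out the BMI stratum.** Let R² be the share of outcome variance that the stratum explains (assumed). After stratified randomisation, the true type I error of an unadjusted nominal 5% test is 2[1 − Φ(1.96/√(1−R²))]. With effect 1 and 19 per group, 1/√(2/19) = 3.08. Power is then Φ((3.08 − 1.96)/√(1−R²)) unadjusted and Φ(3.08/√(1−R²) − 1.96) adjusted.

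| R² | True type I error, unadjusted | Power, unadjusted | Power, adjusted | Loss (points) |
|---|---|---|---|---|
| 5% | 4.4% | 87.5% | 88.5% | 1.0 |
| 10% | 3.9% | 88.2% | 90.1% | 1.9 |
| 20% | 2.8% | 89.5% | 93.1% | 3.6 |

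**The case against.** The strongest reply is that change-score analysis of a randomised trial is valid, that ANCOVA is already in the plan, and that a condensed article may leave the covariate list to a fuller document. Each part has force.

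- **Validity stands.** Regression to the mean acts equally on all groups in expectation. A reader might infer bias from it, but randomisation rules that out on average; what remains is chance imbalance, which is a matter of precision.
- **The loss can be small.** At ρ = 0.9 it is about 5%. In the single-measurement reading, change-score power falls below the planned 80% only at low ρ (74.1% at 0.3). A main effect with no interaction would compare about 38 with 38, so its power is higher than in the tables, although the variance ratio is the same.
- **No method is stated to be primary.** A reader might infer that the primary outcomes will be judged on change scores with ANCOVA in a minor role. The text gives ANCOVA as a between-group comparison in its own right and sets no order.
- **Baseline and stratum are not shown to be discarded.** A change score does use the baseline, and the open ANCOVA wording could take in both the baseline value and BMI.
- **Adjustment for mediators is not planned in the text.** Weight, dietary intake and physical activity are secondary outcomes here, and nothing says that their week-12 values will be covariates. The wording leaves that open, no more.

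A missing covariate list alone would not be a finding. What survives rests on what the section does state: it lists several methods without an order, puts the interaction with change scores, and selects covariates by possible confounding.

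**Conclusion.** The point holds as one of precision and pre-specification, not of bias. The section fixes no primary model for the two gene-expression outcomes and names neither the baseline value nor the BMI stratum in any model. A baseline-adjusted ANCOVA would cut the variance by 35% to 5% over ρ = 0.3 to 0.9, assuming equal variances at the two visits. Leaving out the stratum would make the test conservative (type I error 4.4% to 2.8%) and cost about 1 to 4 points of power, if BMI explains an assumed 5% to 20% of the variance. Neither ρ nor R² is in the protocol, so the actual gain is unknown within these ranges. The documents do not support saying that the baseline is wasted or the stratification ignored. The change is worth making because it costs nothing, but the trial's validity does not depend on it.

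**What to change.** In Statistical methods, name one primary model for each primary outcome: an ANCOVA of the week-12 value on diet, curcumin, diet × curcumin, the baseline value of that outcome and BMI stratum (18.5–25 v 25 or more).

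- For the genes, use the log scale (ΔCt, target minus GAPDH) at both visits and back-transform to fold change for reporting.
- State that covariates in the primary model are limited to variables measured before randomisation.
- Describe the t tests and the change-score ANOVA as descriptive or supportive.

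The cost is wording only. The baseline values and BMI strata are already being collected, and the planned software (SPSS) fits the model.
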